## Abstract

**Introduction:**

A symptom cluster is very common among oncological patients: cancer-related fatigue (CRF), emotional distress, sleep difficulties, pain, and cognitive difficulties. Clinical applications of interventions based on non-ordinary states of consciousness, mostly hypnosis and meditation, are starting to be investigated in oncology settings. They revealed encouraging results in terms of improvements of these symptoms. However, these studies often focused on breast cancer patients, with methodological limitations (e.g., small sample size, no control group, and no follow-up). Another non-ordinary state of consciousness may also have therapeutic applications in oncology: self-induced cognitive trance (SICT). It seems to differ from hypnosis and meditation, as it involves the body more directly. Thus, investigating its clinical applications, along with hypnosis and meditation interventions, could improve available therapeutic options in oncology. This article details the study protocol of a preference-based longitudinal controlled superiority trial aiming to assess the effectiveness of 3 group interventions (hypnosis, meditation, and SICT) to improve oncological patients’ quality of life, and more specifically CRF, emotional distress, sleep, pain, and cognitive difficulties (primary outcomes).

**Methods and analysis:**

A power analysis required a total sample of 160 patients. Main inclusion criteria are: cancer diagnosis, active treatments completed for less than a year, no practice of hypnosis, meditation, or SICT, and presence of at least one of these four symptoms: fatigue, sleep difficulties, depression, or anxiety. Each participant will choose the intervention in which they want to participate (hypnosis, mindful self-compassion meditation, SICT, or no intervention—control group). To test the effectiveness of the interventions, data will be collected by questionnaires and neurobiological measures and directly from the medical record at four time points: before inclusion in the study (baseline); immediately after the intervention; and at 3- and 12-month follow-up. The longitudinal data in each group will then be measured.

**Discussion:**

In addition to standard cancer therapies, there is a growing interest from patients in complementary approaches, such as hypnosis, meditation, and SICT. The results of this study will be useful to increase knowledge about short- and long-term effectiveness of 3 group interventions for CRF, emotional distress, sleep, pain, and cognitive difficulties in patients with different cancers.

**Clinical Trial Registration:**

ClinicalTrials.gov/ (NCT04873661). Retrospectively registered on the 29th of April 2021. url: https://clinicaltrials.gov/ct2/show/NCT04873661

## Introduction

The presence of one symptom cluster is particularly well-documented among patients who suffer from cancer (Dodd et al., 2010; Die Trill, 2013; Loh et al., 2018): cancer-related fatigue (CRF), sleep difficulties, emotional distress, and pain. Cognitive impairments are also frequently associated with this symptom cluster (Pullens et al., 2010; Joly et al., 2011; Sanford et al., 2014). A meta-analysis revealed that 52% of patients report CRF, this proportion ranging from 14 to 100% according to the studies (Ma et al., 2020). CRF can be defined as “a distressing persistent, subjective sense of physical, emotional, and/or cognitive tiredness related to cancer or cancer treatment that is not proportional to recent activity and interferes with usual functioning” (Koh et al., 2019). CRF has a lot of social, financial, and functional consequences (Jones et al., 2016; Ma et al., 2020). Emotional distress, endured by a large proportion of patients with cancer as well (Mehnert et al., 2018; Götze et al., 2020), can be defined as “a multifactorial, unpleasant experience of a psychologic (i.e., cognitive, behavioral, and emotional), social, spiritual, and/or physical nature that may interfere with the ability to cope effectively with cancer, its physical symptoms, and its treatment” (Mitchell et al., 2011; Riba et al., 2019). It negatively influences treatment adherence (Lin et al., 2017) and results (Batty et al., 2017), as well as patient’s general quality of life (Achimas-Cadariu et al., 2015; Riba et al., 2019). Concerning sleep difficulties, their prevalence among patients with cancer during or after their treatment varies between 32 and 61% (Santoso et al., 2019; Schieber et al., 2019; Hoang et al., 2020; Gonzalez et al., 2021) and is approximately three times higher than in the general population (Kwak et al., 2020). Cancer-related pain is reported by more than 50% of patients, which severely impacts quality of life, adherence to treatment, satisfaction with care, and survival (Neufeld et al., 2017). Finally, cognitive difficulties may be linked to the disease itself, the treatments received or the patient characteristics, and their prevalence can be up to 75% in some kinds of cancers (Joly et al., 2011).

All these difficulties can last for years after treatment completion and, despite their prevalence and severe impact, they remain underdiagnosed and undertreated (Joly et al., 2011; Die Trill, 2013; de Vries and Stiefel, 2014; Riba et al., 2019). In oncology settings, there is a growing interest in complementary approaches, such as “mind–body” interventions, to relieve these symptoms in a non-pharmacological way. These interventions aim to impact two interconnected levels: psychological and physical (Sawni and Breuner, 2017), and they allow patients to take back the control over their health and to regain hope (Eliott et al., 2008). Indeed, complementary and alternative medicine is estimated to be used by 43% of patients with cancer (Horneber et al., 2012; John et al., 2016), and it is starting to be studied scientifically, for instance with trials investigating the benefits of hypnosis and meditation (Spiegel, 1985; Kim et al., 2013; Cramer et al., 2015; Carlson et al., 2017; Grégoire et al., 2017, 2020a; Arring et al., 2019; Ngamkham et al., 2019; Suh et al., 2021).

### Hypnosis

**Hypnosis** can be defined as “a state of consciousness involving focused attention and reduced peripheral awareness characterized by an enhanced capacity for response to suggestion” (Elkins et al., 2015). It is characterized by four main components: absorption (in an imaginative experience), dissociation (from the environment), suggestibility (to the suggestions made by the therapist; Spiegel, 1991), and automaticity (non-voluntary response relevant to the content of a communication intended to be a suggestion; Weitzenhoffer, 2002). Hypnosis modulates self-awareness and decreases environmental awareness (Demertzi et al., 2011, 2015). At a neurophysiological level, it is associated with increased power in the theta band and changes in gamma activity (direction inconsistent among studies), which play a critical role in the emotional limbic circuits (Vanhaudenhuyse et al., 2020). Hypnosis also modifies the functional connectivity in the default mode network (linked to self-awareness) and in the external network (linked to the environmental awareness; Vanhaudenhuyse et al., 2014), as well as the structural connectivity between brain areas, and the hemispheric asymmetry (Landry et al., 2017). It also impacts cortical and subcortical areas involved in pain modulation (Vanhaudenhuyse et al., 2014; De Benedittis, 2021; Bicego et al., 2021c).

To summarize empirical findings about hypnosis mechanisms, Jensen et al. proposed a biopsychosocial model of hypnosis (Jensen et al., 2015). Three categories of factors explained hypnotic responding: biological factors (activity in frontal and anterior cingulate cortices, functional connectivity, structural connectivity, hemisphere asymmetry, and theta band), psychological factors (expectancies, hypnotizability, motivation, and absorption), and social factors (relationship with the therapist and hypnotic context). Several studies have demonstrated the benefits of hypnosis, used alone or in combination with other techniques, on different sides effects of cancer treatments, such as CRF, emotional distress, sleep, pain, and cognitive difficulties (Spiegel, 1985; Cramer et al., 2015; Carlson et al., 2017; Grégoire et al., 2017, 2020a; Arring et al., 2019).

### Meditation

Similarly to hypnosis, **meditation** is also considered a non-ordinary state of consciousness. It can be defined as a group of “states, processes, and practices that self-regulate the body and mind, thereby affecting mental and physical events by engaging a specific attentional set” (De Benedittis, 2015). Its aim is to improve voluntary control over mental processes. Different meditation practices exist, with similarities: a quiet location with few distractions, a specific and comfortable posture (sitting or lying down), a focus on attention, and an open attitude of letting thoughts come and go without judgment (Ospina et al., 2008). Phenomenological characteristics of meditation vary according to the type of practice, but alteration of sense of time, space and body representation, along with modifications of emotions and physical sensations are commonly reported (Brandmeyer et al., 2019). The neurophysiological correlates of mediation also depend on the type of meditation and thus are not yet clear (De Benedittis, 2015; Lomas, 2015; Brandmeyer et al., 2019). However, a systematic review showed that mindfulness-based meditation is associated with increased alpha and theta power, while no consistent patterns were observed in beta, delta, and gamma bandwidths. This configuration is indicative of a state of relaxed alertness favoring mental health (Lomas, 2015; Brandmeyer et al., 2019). Meditation has also been shown to positively influence emotional distress, pain, fatigue, and sleep difficulties in patients with cancer (Kim et al., 2013; Carlson et al., 2017; Arring et al., 2019; Ngamkham et al., 2019; Suh et al., 2021). Our study will focus on mindful self-compassion (MSC) meditation (Kotsou and Heeren, 2011; Germer and Neff, 2013, 2019; Neff and Germer, 2013; Neff et al., 2020), which involves a compassionate stance toward oneself when encountering personal difficulties (i.e., self-kindness over self-judgment, sense of common humanity instead of isolation, and mindfulness rather than over-identification), and has been shown to positively influence psychological wellbeing (Kotsou and Leys, 2016; Kılıç et al., 2021). This self-compassionate frame of mind involves being gentle, supportive, accepting, and understanding toward oneself (Germer and Neff, 2019).

Most of these studies about hypnosis and meditation suffer from methodological limitations, the main one being their focus on breast cancer patients only. However, other cancers may have different negative physical and psychological effects. For example, mortality rates vary according to the localization of the tumor (Sung et al., 2021). Additionally, some cancers imply specific adverse events [e.g., prostate cancers (impact on sexuality, possible urinary incontinence) and head and neck cancers (possible tracheotomy with impact on speech)], which may have specific impact on the psychological adaptation to the disease. In addition, most of these studies did not measure the long-term effects of the intervention proposed.

In this study, our aim will be to include a large population of patients with different cancer diagnoses and to rigorously investigate the long-term effects of the interventions. We also want to study another non-ordinary state of consciousness, involving more directly the body: self-induced cognitive trance.

### Self-Induced Cognitive Trance

The recent work on hypnosis and meditation has opened the path to study other non-ordinary states of consciousness, such as trance. Self-induced cognitive trance (SICT) is characterized by lucid but narrowed awareness of the environment, hyper-focused immersive experience of flow, enhanced inner imagery, modified somatosensory processing, altered sense of self, and an experience of spiritual travel (Csikszentmihalyi, 1990; Flor-Henry et al., 2017; Grégoire et al., 2021). It is inherited from Mongolian traditional shamanic practice, where is it used in healing interventions (Flor-Henry et al., 2017; Grégoire et al., 2021). However, little is known about the scientifically based phenomenology and neural correlates of SICT. A few case studies report that it is associated with subjective changes in time and space perception, body awareness, thinking and emotional state, with a dissociation and a modulation of perceptions from the environment, as well as decreased pain perception, increased strength, increased sense of happiness, visual imagery, and out-of-body experience (Hove et al., 2016; Flor-Henry et al., 2017; Kawai et al., 2017; Mainieri et al., 2017; Gosseries et al., 2020; Huels et al., 2021). This could be put in parallel with some of the characteristics of hypnosis already described (absorption, dissociation, and modulation of pain, for examples; Vanhaudenhuyse et al., 2014, 2020). Only a few studies used neurophysiological measurements during different kinds of trance, including SICT (Oohashi et al., 2002; Peres et al., 2012; Hove et al., 2016; Flor-Henry et al., 2017; Gosseries et al., 2020), and showed a temporary reconfiguration of brain network architecture. However, results are quite contradictory, and studies are mostly from small samples of trance experts with a lack of well-controlled designs. Moreover, no study has evaluated the clinical applications of SICT, even though it may have potential therapeutic properties, like hypnosis and meditation. Previous works on shamanic trance have reported positive outcomes (e.g., decrease anxiety and increase wellbeing) anecdotally, but not scientifically (Sidky, 2009; Mackinnon, 2012; Grégoire et al., 2021). Thus, investigating SICT’s phenomenological and neurophysiological correlates, as well as its clinical applications, and comparing them with hypnosis and meditation interventions seems particularly relevant as it will allow to better understand these non-ordinary states of consciousness and improve available complementary therapeutic options in oncology.

## Objectives

This project’s aims are threefold: (1) Evaluating the short- and long-term clinical benefits of hypnosis, meditation, and SICT in terms of CRF, emotional distress, sleep difficulties, and pain (primary outcomes), as well as other psychological variables (e.g., cognitive functioning, adaptation to cancer, psychological flexibility; secondary outcomes) in patients with cancer (through questionnaires); (2) Measuring the evolution of (a) phenomenological and (b) neurobiological correlates of hypnosis, meditation, and SICT in these patients, to better understand the effects of these interventions (through questionnaires and neurobiological measures); (3) Confirming the biopsychosocial model of hypnosis and investigating whether meditation and SICT responsiveness are mediated by the same mechanisms as hypnosis. This study will allow to strengthen the use of hypnosis and meditation for all cancers and to assess the interest of SICT as a new therapeutic complementary option.

## Methods and Analysis

### Design

We designed a longitudinal controlled superiority trial (see Figure 1) with 160 patients with cancer who will choose between four conditions (see section “Recruitment” for sample size calculation): hypnosis-based group intervention, MSC meditation-based group intervention, SICT-based group intervention, or a control group. This kind of design has been chosen because patients who receive their preferred therapeutic option seem to be more motivated and exhibit greater adherence to the treatment (King et al., 2005; Preference Collaborative Review Group, 2008; Sedgwick, 2013; Bicego et al., 2021a). Indeed, preference-based trials are increasingly developed as researchers often want to know if an intervention is effective for the participants who choose it, rather than determining the best treatment option irrespective of the participant’s choice (Kowalski and Mrdjenovich, 2013). In addition, pragmatic trials are also more and more developed and aim at assessing the effects of interventions in real-life routine practice conditions, rather than under optimal conditions. The results from a pragmatic trial can be generalized and applied in routine practice (Patsopoulos, 2011). Moreover, one of our previous study with oncological patients showed that different intervention groups, based on participants’ preferences, were similar at baseline on the sociodemographic, medical, and clinical data investigated (Grégoire et al., 2017). Participants will then know in which group they belong and will be aware of the existence of the other intervention groups.

**Figure 1 fig1:**
[figure not shown]
Study design. SICT, self-induced cognitive trance; MSC, mindful self-compassion; hrs, hours.

The structure and intensity of each intervention will be different (see Figure 1), because we want to optimize the trainings in a manner that has been shown to be effective in our practice with volunteers and patients (Grégoire et al., 2017, 2018b). More specifically, in the hypnosis-based intervention, patients will participate in 8 weekly sessions (2 h each) during which they will benefit from guided hypnosis exercises and learn how to implement self-hypnosis in their daily life. In the MSC meditation-based intervention, patients will participate in 8 weekly sessions (2 h45 each) and half a day of intensive practice, in which they will practice different meditation exercises. In the SICT-based intervention, patients will participate in 2-day workshops, spaced by 2 weeks, in which they will learn how to induce SICT, with the use of different sound loops (i.e., electronic designed sounds, voices, and noises). In the three groups, exercises will mostly focus on self-compassion as this component has been shown to be important in oncology settings in previous studies (Grégoire et al., 2017, 2018b, 2020a). At-home practice will also be encouraged between sessions and will be assessed through weekly evaluations (see Table 1 for measurements used). Participants in the control group will complete the questionnaires and undergo the neurobiological examinations, but they will not attend any of the interventions. They will only benefit from care as usual and have the possibility to participate in one of the three group interventions after the study completion if they want to. More information about the content of each intervention is detailed in section “Interventions”.

**Table 1 tab1:** Measurements used in the study.

	Screening	T0	Between T0 and T1 (during the group intervention)	T1	T2	T3
**Medical data**: diagnosis, time since the end of treatments, psychiatric and neurologic history	X					
**VAS**: fatigue, distress, pain, sleep difficulties (/10)	X					
**No practice** of hypnosis, meditation or SICT	X					
**Sociodemographic data**: age, gender, religious beliefs, professional status, BFI-10		X				
**Medical data**: time since diagnosis, cancer stage, treatment received		X				
**Weekly subjective evaluations** (VAS fatigue, emotional distress, sleep difficulties, pain)			X			
**Diary of practice** (frequency, details about some intense episodes, feelings, impressions, etc.)			X			
**Hypnosis/meditation/SICT and imaginary experience**: •VAS (/10): expectations, motivation to experience hypnosis/meditation/SICT^*^ •Personal definition and *a priori* according to the chosen intervention (free text)^*^ •CEQ		X				
**Quality of life-related variables**: •Fatigue and sleep: MFI20 and ISI •Emotional distress: HADS •Pain: VAS (/10) •Self-reported cognitive functioning: FACT-Cog v3 •Other psychological variables: MAC, CERQ, MPFI-24, Empowerment [7 VAS (/10)], major life events		X		X	X	X
**Neurophysiological and biological variables**: •EEG resting state		X		X		X
•EEG during hypnosis, meditation or SICT state^*^				X		X
•ECG, EMG, and respiration (effort and pressure)		X		X		X
•Core body temperature		X		X		X
•Tumor marker rates		X		X		X
**Questionnaires about the intervention**: •Free recall of a hypnosis/meditation/SICT/intense autobiographical episode (written, according to the intervention) •MCQ •MEQ30 •Presence questionnaire •VAS (/10): Quality of the relationship with the therapist^*^				X	X	X

BFI, Big Five Inventory; CEQ, Creative Experiences Questionnaire; CERQ, Cognitive Emotion Regulation Questionnaire; FACT-Cog, Functional Assessment of Cancer Therapy – Cognitive Function; HADS, Hospital Anxiety and Depression Scale; ISI, Insomnia Severity Index; MAC, Mental Adjustment to Cancer Scale; MCQ-30, Memory Characteristics Questionnaire; MEQ30, Revised Mystical Experience Questionnaire; MFI-20, Multidimensional Fatigue Inventory; MPFI-24, Multidimensional Psychological Flexibility Index; ECG, electrocardiogram; EEG, electroencephalogram; EMG, electromyogram; VAS, Visual Analogue Scale.

* Only for the participants in one of the 3 intervention groups.

Each participant from the three intervention groups will be evaluated before the intervention (T0), right after the last group session (T1), at 3 months (T2) and 1 year (T3) post-intervention. Participants in the control group will be evaluated according to a similar schedule (see Figure 1 for study design, and sections “Procedures” and “Assessments” for more information on procedures and measurements). The first intervention group (hypnosis) started in April 2021.

### Eligibility

Inclusion criteria will be: to be at least 18 years old, no psychiatric or neurological disorders, no current and regular practice of hypnosis, meditation or trance, diagnosis of cancer (any localization except brain tumors to avoid any effect on EEG data or severe cognitive impairments that could prevent filling the questionnaires adequately), and completion of active treatments (surgery, chemotherapy, radiotherapy) for less than a year. Interested patients will be screened for fatigue, emotional distress, sleep difficulties, and pain (VAS score ≥ 4/10 for one of these four symptoms for inclusion), based on recommendations from our past studies (Grégoire et al., 2018a,b).

### Recruitment

Participants will be recruited over a 2- to 3-year period, mainly at the University Hospital of Liège (Belgium) but also in other structures and through social medias. Potentially eligible participants will be identified in various ways. First, different health care professionals working with oncological patients (e.g., oncologists, radiotherapists, psychologists, nurses) have been informed of the study and asked to talk about it to their patients who have completed their treatment. In the hospital, interested patients will be advised to contact us by phone or e-mail. Second, flyers and posters will be displayed in several strategic areas in and outside the hospital (e.g., oncology, radiotherapy, algology services’ waiting rooms, doctors’ office, private consultations cabinet, other hospitals, health associations, health professionals in Belgium or France), which allow other health professionals and patients to be informed about our study. Third, we will use social medias (e.g., personal and professional Facebook accounts, Mewe) to inform as much people as possible about our study.

The recruitment started in December 2020 and is ongoing. Sample size has been determined by a power analysis allowing a comparison between the four groups. The sample size calculation was based on a repeated measures ANOVA (“between factors”). Alpha was set at 0.05, power at 90%, the standardized effect size at 0.3 and the expected correlation between repeated measures at 0.6. These coefficients were successfully used in our previous studies (Grégoire et al., 2017, 2020a). As there will be four groups and four measurements times, a total of 116 patients will be needed according to this analysis. Based on our previous experience with a similar design, we expect a 20% drop-out rate, leading to a sample of 140 patients (35 in each condition; Grégoire et al., 2020a). As our group sessions will include approximately 10 persons, we will then aim at recruiting 40 participants in each condition (i.e., four groups of 10 participants in hypnosis, MSC meditation, and SICT groups and 40 participants in the control group), for a final sample of 160 participants. Participants will have the opportunity to choose the intervention in which they want to participate. Most of the participants already have a strong preference for one of the three interventions when contacting us. However, each interested person who fill the inclusion criteria will be asked to watch a short video we made to explain the three interventions and the aims of the study.^1^ This allows every participant to receive standardized information about the study and to make or confirm their choice of intervention. However, once 40 participants have been recruited in a condition, it will not be possible for other interested persons to be included in this condition. These persons will be proposed to integrate the control group or another active condition.

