### Interventions

#### Hypnosis

This intervention will include eight 2h weekly sessions in groups of approximately 10 participants. This protocol has been developed and will be led by one of the authors ([name]), who is an anesthesiologist and an international expert in hypnosis. A large part of the first session will be devoted to answering to the participants’ questions and giving information about hypnosis. First exercises will be proposed as introduction to hypnosis: a focused listening of different musical records and some imagery exercises. The aim is for the participants to notice their abilities to access mental imagery and hypnosis. During the other sessions, a debriefing of at-home practice will be proposed, along with different hypnosis exercises. They will be repeated and discussed, and participants will also attempt to induce hypnosis by themselves during the last session. Table 2 summarizes the exercises that will be done at each session. Between sessions, participants will be encouraged to practice the different exercises at home with the help of audio recordings of the hypnosis exercises. This is essential to take full advantage of hypnosis without the help of a therapist. A self-care approach will be fostered during the intervention, more specifically during the debriefings of the participants’ practice, if they encounter difficulties or ruminations. Concrete strategies to deal with such difficulties will be proposed by the therapist. The importance to take time for themselves will be emphasized, as well as to allow themselves to take a break from their routine and practice hypnosis in their daily life to improve their wellbeing, in an adaptation of our usual practice with oncological patients in clinical and experimental settings (Charland-Verville et al., 2017; Grégoire et al., 2018b, 2020a).

**Table 2 tab2:** Summary of the content of the sessions for each intervention.

	Hypnosis	MSC meditation		Self-induced cognitive trance (SICT)

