### Statistical Analyses

Baseline (T0) demographic, medical, and psychological data will be compared between groups to test for initial groups equivalency using inferential statistics, including ANOVAs and chi-square tests. Normality of data will be checked using Shapiro–Wilk test. Group-by time changes, and pre- and post-assessment comparison of each variable within each group will be assessed using repeated measures MANOVA followed by post hoc comparisons, on the participants who completed all the needed assessments points. Hierarchical linear regressions will be conducted to investigate the factors associated with the evolution of our main outcomes. All tests will be two-tailed, and the alpha will be set at 0.05. For EEG data analysis, MATLAB, EEGLAB, FieldTrip, Brainstorm, and in-house MATLAB and Python modules will be used. EEG signal will be preprocessed as in our previous works [downsampling, epoching, filtering, removing noise (notably using ICA), channels interpolation, re-referencing; Carrière et al., 2020; Thibaut et al., 2021]. EEG markers will then be extracted: spectral (e.g., power spectrum density), connectivity (e.g., weighted symmetrical mutual information), complexity (e.g., permutation entropy; Engemann et al., 2018). We will also apply graph theory connectivity measures to further assess changes between brain regions (Chennu et al., 2017; Carrière et al., 2020; Thibaut et al., 2021). Results will be corrected for multiple comparisons and considered significant at *p* < 0.05. Statistical analyses will be performed after all data have been collected for T2, then for T3 and T4.

All participants will be informed by e-mail about the final results of the study. Scientific publications and presentations will also be planned.

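### Active arms are treated in session groups of about 10, but the sample size and the planned test assume independent participants, so type I error exceeds 5% if session groups differ

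*Protocol article*

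**What the plan says.** **Delivery.** The Recruitment section of the protocol article plans "four groups of 10 participants in hypnosis, MSC meditation, and SICT groups and 40 participants in the control group". The Hypnosis section repeats that the sessions run "in groups of approximately 10 participants", and the MSC Meditation and Self-Induced Cognitive Trance sections give the same group size. All three interventions include debriefing within the group. Under Screening, T0 is scheduled once a group is nearly full, so its members also go through the study together. The Design section says that controls attend none of the interventions.

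**Sample size.** Recruitment uses the between-factors test of a repeated measures ANOVA: "Alpha was set at 0.05, power at 90%, the standardized effect size at 0.3 and the expected correlation between repeated measures at 0.6". The result is 116, raised to 140 for dropout. The session-group size enters only when 35 per condition is rounded up to 40, giving 160.

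**Analysis.** Statistical Analyses states: "Group-by time changes, and pre- and post-assessment comparison of each variable within each group will be assessed using repeated measures MANOVA". Post hoc comparisons follow, in participants with all the required assessments, and "All tests will be two-tailed, and the alpha will be set at 0.05". Neither section has an ICC, a design effect, a session-group term or cluster-robust standard errors.

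**The concern.** The design is partially nested: about four clusters in each active arm, and unclustered individuals in the control arm. People who learn together, discuss their difficulties together and pass through the same months tend to have correlated outcomes afterwards. The only correlation in the plan is "the expected correlation between repeated measures at 0.6", which concerns one person's scores over time and says nothing about people in the same session group.

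If that correlation is positive, an arm mean varies more than the planned test assumes. The group-by-time test and the post hoc comparisons then reject too often. Comparisons between two interventions are affected more than comparisons with control, because both sides are clustered. Filling the same four groups with more people does not remove the problem.

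**Working it through.** **1. The plan's own figure.** Inputs from Recruitment: f = 0.3 (the stated effect size, read as Cohen's f), k = 4 conditions, m = 4 time points, ρ = 0.6, α = 0.05.

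λ = f²·N·m / [1 + (m − 1)ρ] = 0.09 × 116 × 4 / 2.8 = 14.91, with 3 and 112 degrees of freedom. Power is 0.905. The smallest N that reaches 90% is 115, or 116 in equal groups. The figure therefore reproduces, with participants taken as independent.

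**2. Size of the analysed clusters.** The analysis uses completers and the plan expects 20% dropout: 160 × 0.8 = 128 completers, 32 per arm, 32 / 4 = 8 per session group. Under independence, power at N = 128 is 0.93.

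**3. Hand check on a post-intervention score.** The ICC is assumed. The design effect is DE = 1 + (8 − 1) × ICC. The true standard error divided by the assumed one is √[(DE + 1)/2] for active versus control and √DE for active versus active.

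| ICC | DE | 32 / DE | SE ratio, active v control | SE ratio, active v active |
|---|---|---|---|---|
| 0.01 | 1.07 | 29.9 | 1.02 | 1.03 |
| 0.02 | 1.14 | 28.1 | 1.03 | 1.07 |
| 0.05 | 1.35 | 23.7 | 1.08 | 1.16 |
| 0.10 | 1.70 | 18.8 | 1.16 | 1.30 |

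At ICC 0.05 the normal approximation to the two-sided error is 2[1 − Φ(1.96/1.084)] = 7.1% against control and 2[1 − Φ(1.96/1.162)] = 9.2% between interventions.

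**4. Simulated type I error at nominal 5%.** Three arms of four session groups of 8, plus 32 unclustered controls. Two tests were examined:
- the group-by-time test on one outcome, with ρ = 0.6 and the session-group effect acting at T1 to T3 only (6,000 to 8,000 trials per setting);
- the between-group tests on each person's mean score (30,000 trials per setting).

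| ICC | Group-by-time | Omnibus, person means | Active v control, person means | Active v active, person means |
|---|---|---|---|---|
| 0 | 5.2% | 4.8% | 5.1% | 4.8% |
| 0.01 | 5-6% | 5.9% | 5.4% | 5.7% |
| 0.02 | 7% | 7.0% | 5.8% | 6.5% |
| 0.05 | 10-11% | 10.5% | 7.0% | 9.7% |
| 0.10 | 17-18% | 16.4% | 9.1% | 13.6% |

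The ICC = 0 row returns the nominal level. For the change from T0 to T1 at ICC 0.05, the errors are 7.7% against control and 9.8% between interventions, in line with step 3.

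**5. Power with the test held at a true 5%.** Between-group test on person means, 32 completers per arm, the three active arms equal and control different, effect matched to f = 0.3: 0.925 (ICC 0.01), 0.915 (0.02), 0.88 (0.05) and 0.81 (0.10). These are optimistic, because a valid analysis with four clusters per arm has few degrees of freedom for the session-group variance.

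**The case against.** **A condensed article may leave the random-effects structure to a fuller plan.** That would hold if the article were silent. It names the sample size model with its inputs and the main test, and session groups cannot be added without departing from that test. The hierarchical linear regressions in the same section are for factors associated with change in the outcomes and are not described as modelling session groups.

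**The size is unknown.** This stands. At ICC 0.01 the effect is small, and a reader might infer from the rows for 0.05 and 0.10 that false positives will double or triple. The documents give no ICC and do not support that as a prediction.

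**A reader might infer that the trial is underpowered and its 90% wrong.** The documents do not support this as a general statement. The 90% belongs to 116, and 160 are to be recruited. That margin absorbs much of the loss, and all of it at an ICC of 0.02 or less on the figures above.

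**A reader might infer that a shared leader causes the clustering.** The Hypnosis and MSC Meditation sections give the same leader or leaders for the whole arm. Such an effect is confounded with arm. It does not make session groups within the arm differ, and a session-group term does not remove it. Standard content and a common leader could even argue for a small ICC.

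**Self-selection into arms is the larger threat.** Perhaps so, and the Discussion acknowledges the lack of randomisation. That concerns bias; this point concerns the validity of standard errors and p-values, and remains after any handling of selection.

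**Conclusion.** The point holds, conditionally in its size. The plan creates about 12 session groups in the active arms and ignores them in both the sample size and the main test. Type I error is the main harm: negligible to slight at an ICC of 0.01 to 0.02, and about double the nominal level for the group-by-time test at 0.05. Comparisons with control, which carry the superiority hypothesis, are affected less (about 7-8% at 0.05) than comparisons between interventions (about 10%). The power loss is secondary.

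These figures assume an ICC of 0.01 to 0.10, session-group effects that arise after T0, and 8 completers in each of four groups per arm. The defect can be repaired at the analysis stage, provided that session-group membership is kept.

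**What to change.** - Record the session-group identifier for every active-arm participant.
- In Statistical Analyses, replace the repeated measures MANOVA with a partially nested linear mixed model: a random session-group effect in the three active arms only, controls entered as singletons, and Kenward-Roger or Satterthwaite degrees of freedom. Take the pairwise comparisons from the same model.
- In Recruitment, restate the power for the completers expected from 160, over an assumed ICC range such as 0.01 to 0.10.

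**Cost.** Recruitment and delivery need not change, but the primary analysis method does. Intervals widen and the stated power looks less favourable. With four clusters per arm the session-group variance will be poorly estimated and may come out as zero, in which case the model gives little protection. The change does not separate the effect of an intervention from that of a leader common to its arm.
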